### Western medicine intervention

4.2

Besides, if necessary patients in the 2 groups could be given nitroglycerin (allowed to be taken at a dose of 0.5 g sublingual) as other common western medical treating.

### Forbidden treatments and drugs combination

4.3

1.Any other TCM methods are not allowed (herbs except for THJG or THJG placebo, acupuncture, cupping, plaster, etc).2.In the run-in and study period, usage of aspirin, BBs, CCBs, nitrates except for nitroglycerin and lipid-lowering drugs, in the previous 4 weeks is allowed to continue and alteration is proscribed.3.The dosage, duration, and name of any intervention must be recorded thoroughly in the case report forms (CRFs).

### Randomization and allocation

4.4

Shanghai Medical Clinical Research Center (CRC, website: http://www.scrcnet.org) will control the randomization and create a random number listing by SAS 9.1 PROC PLAN. This list contains 2 matching groups: 1st group is sequence number of inclusion, 2nd is the THJG or placebo group.

Pharmaceutical factory will call the CRC to acquire the random number listing after completing drugs, then attach the sequence number to boxes of medicine (THJG or placebo) according to the listing. Medicine will be transported to the CRC, administrated by a trained staff.

All the investigators (except for the CRC and pharmaceutical factory) will not know the corresponding relations between sequence numbers and different groups until the trials are completed.

When a participant is eligible to be included, the investigator will make a central telephone call and give him/her the medicine (THJG or the placebo) from the CRC administrator according to the central call.

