### Study design

2.1

This is a multicenter, randomized, double-blinded, placebo-controlled clinical trial with 2 parallel arms. The purpose of this research is to estimate the effectiveness and safety of THJG combined in administrate SCAD symptoms and inflammation. Altogether, we will recruit 80 patients with SCAD from 3 hospitals in China: LongHua Hospital affiliated to Shanghai University of Traditional Chinese Medicine, Shanghai Seventh People's Hospital, Gongli Hospital of Shanghai Pudong New Area, Shanggang Community Health Service Center of Shanghai Pudong New Area. Eighty participants will be randomized into THJG group or placebo group according to patients’ included sequence number equally. Patients in THJG group will take THJG (18.3 g, twice a day, orally) for continuous 4 weeks, while patients in placebo group will take THJG placebo (18.3 g, twice a day, orally) for the same duration. The Standard Protocol Items: Recommendation for Interventional Trials SPIRIT 2013 Checklist (Supplementary Material file 1).

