### Study participants

2.3

Participants will be recruited from 3 hospitals (LongHua Hospital affiliated to Shanghai University of Traditional Chinese Medicine, Gongli Hospital of Shanghai Pudong New Area, Shanggang Community Health Service Center of Shanghai Pudong New Area). Recruitment posters and social application advertisements will be proclaimed. The objective, approaches, and potential side-effects and advantages of this research will be explicated utterly to the participants before participants signing informed consent. The planned enrollment period is 15 months.

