#### Integral TCM syndrome score (from baseline to week 4)

5.1.1

Integral TCM syndrome score is a widely used system to evaluate the efficacy of Chinese herb treating SCAD patients, which are stagnant Qi and blood type in China.^[11]^ This assessment form is constitutive of 2 parts: symptom part and sign part. In detail, there are total 8 appraisable items, angina, chest distress, palpitation, vexation, insomnia, lassitude, dizziness, and color of lips and snails, respectively. Each item consists of 4 levels and regarding scores. Wholly, the minimum score is 0 and the maximum score is 33. The higher scores of participants mean a severer condition. The scores and details of TCM syndrome are given in Tables 2 and 3.

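### Allocation follows the inclusion number with no mention of centre, so the arm split within each centre is left to chance: a modest, avoidable loss of precision and interpretability, not bias

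*Protocol article*

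**What the plan says.** Section 4.4 has the clinical research centre (CRC) produce the list with SAS PROC PLAN and describes its content: "This list contains 2 matching groups: 1st group is sequence number of inclusion, 2nd is the THJG or placebo group". The factory is then to "attach the sequence number to boxes of medicine (THJG or placebo) according to the listing". For each eligible patient "the investigator will make a central telephone call and give him/her the medicine (THJG or the placebo) from the CRC administrator".

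Study design (2.1) gives the same basis for allocation: "Eighty participants will be randomized into THJG group or placebo group according to patients’ included sequence number equally". Neither section mentions centre, strata or number ranges reserved for a centre.

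On sites, Study participants (2.3) says "Participants will be recruited from 3 hospitals" and lists a university-affiliated hospital plus "Gongli Hospital of Shanghai Pudong New Area, Shanggang Community Health Service Center of Shanghai Pudong New Area". Study design also says three hospitals but names four sites.

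The primary outcome (5.1.1) is an eight-item score from 0 to 33, each item graded on four levels: "This assessment form is constitutive of 2 parts: symptom part and sign part". It is labelled as running from baseline to week 4. Statistical analysis (5.8) names a Student t test, or a nonparametric test if the data are not normal, with no centre term.

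**The concern.** A list that is balanced only over all 80 patients does not control the split inside any one centre. The sites appear to range from a teaching hospital to a community health centre, and the primary score depends on graded symptoms and an inspected sign. Severity, grading habits or response to treatment could differ by site. If they do, a lopsided split at one site adds chance variation to the arm comparison. It also invites the question whether a result reflects the granule or the site. Because assignment already runs through a central call and centrally held stock, this could be prevented cheaply.

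**Working it through.** **Inputs from the protocol.** 80 patients, 40 per arm, difference 4, SD 7.7, two-sided 5% (Sample size calculation, 5.7); allocation by inclusion number (2.1, 4.4). **Assumed, because the protocol does not give them:** patients per centre and the size of any centre difference.

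**1. The plan's own figures.** It gives none for balance by centre. Its sample size matters only as the baseline for power. The stated inputs give 2 × 7.7² × (1.96 + 1.282)² / 4² = 77.9, so 78 per arm. With 40 per arm, power is 64% (63% by noncentral t), not 90%. That mismatch is a separate matter, but it explains why the powers in step 5 are near 63%.

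**2. Split within one centre.** Under one list with 40 per arm overall, the number on THJG in a centre of n patients is hypergeometric (80, 40, n). For n = 27:
- SD = √(27 × ½ × ½ × 53/79) = 2.13.
- P(17:10 or worse, either direction) = 0.155.
- P(18:9 or worse) = 0.058.

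The chance of 2:1 or worse in a given centre is 31% for 10 patients, 16% for 16, 7% for 20, 6% for 27 and 0.3% for 40.

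**3. Shift in the arm difference.** Let one centre of 27 score c points higher than the rest, and let X of its patients receive THJG. The shift is c × (2X − 27)/40, with SD c × 2 × 2.13/40. This is 0.21, 0.43 and 0.64 points for c = 2, 4 and 6. The planned standard error is 7.7 × √(2/40) = 1.72. These shifts apply to raw week-4 scores. In change from baseline, a constant offset is subtracted from itself within each patient and disappears; only a centre difference in change would remain.

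**4. Any centre, several layouts.** Simulation with 8,000 lists per row; a 4-point difference is placed in the last-listed centre.

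| Centre sizes | Some centre 2:1 or worse: overall list | Same: blocks of 4 within centre | SD of shift: overall list | SD of shift: within centre |
|---|---|---|---|---|
| 27/27/26 | 12% | 0% | 0.42 | 0.09 |
| 40/24/16 | 22-23% | 0% | 0.36 | 0.00 |
| 20 × 4 | 22-23% | 0% | 0.39 | 0.00 |
| 40/20/10/10 | 55% | 0% | 0.30 | 0.10 |

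The 95th percentile of the absolute shift falls from 0.6-0.8 to 0-0.2 points. Using blocks of 4 on the overall list gives almost the same figures as an unblocked overall list.

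**5. Error rate and power.** Centre sizes 40/24/16, offsets 0, 2 and 6, total SD held at 7.7. The mean offset is 0.5 × 0 + 0.3 × 2 + 0.2 × 6 = 1.8. The between-centre variance is 0.5 × 1.8² + 0.3 × 0.2² + 0.2 × 4.2² = 5.16, so the within-centre SD is √(59.29 − 5.16) = 7.36. There were 6,000 runs per cell.

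| List | Analysis | Type I error | Power |
|---|---|---|---|
| Overall | t test | 5.2% | 63% |
| Overall | centre-adjusted | 4.7% | 66% |
| Within centre | t test | 3.8% | 62% |
| Within centre | centre-adjusted | 4.9% | 66% |

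Monte Carlo standard errors are √(0.05 × 0.95/6000) = 0.3 percentage points for type I error and √(0.63 × 0.37/6000) = 0.6 for power. The 3.8% is therefore clearly below 5%. The two adjusted analyses do not differ in power.

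**The case against.** The strongest reply is that the protocol makes no error here. Chance imbalance under valid randomisation is already allowed for by the t test, and staff are blinded, so grading habits cannot follow treatment. Quality control (5.6) provides joint training and weekly visits to each centre. That stands. A reader might infer that a lopsided centre biases the result or inflates false positives; the simulated 5.2% does not support this.

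A reader might also infer that the protocol commits to a single unstratified list. That is the natural reading of both sections, but neither says so outright, and number ranges reserved per centre would fit the same sentences. An article may leave stratum details and a centre term to fuller documents, so their absence alone is no fault. What can be held against the text is that it describes an allocation basis and a test, and centre enters neither.

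Third, the shift of 0.43 points needs raw week-4 scores. The outcome's label suggests change from baseline, in which a constant difference in severity or grading cancels. The noise should not be counted twice either. If 7.7 is the total SD, centre variance already lies within the 1.72: a 4-point offset in 27 of 80 patients contributes 16 × (27/80) × (53/80) = 3.6 of 59.3, or 6%, and removing it cuts the standard error by about 3%.

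Finally, a reader might infer that stratifying the list restores power. It does not: with a plain t test, power is 62% against 63%. That the centres differ strongly is likewise inferred from their names; the protocol gives no centre-level data.

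**Conclusion.** The point holds in a limited form. As described, allocation and test both leave centre out, so balance within centres is left to chance. A split of 2:1 or worse somewhere has a probability of 12% with near-equal centres and up to 55% in the most uneven layout tried. With a 4-point centre difference in the analysed quantity, the chance shift has an SD of 0.30-0.43 points and a 95th percentile of 0.6-0.8, against a target difference of 4. The consequence is a small loss of precision, about 3 percentage points of power under the assumed offsets and none if centres do not differ, and a result that is harder to interpret if one centre is lopsided. Centre sizes and offsets are assumptions throughout. This is a worthwhile refinement, not a threat to validity.

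**What to change.** 1. Reconcile the site list first: Study design states three hospitals and names four sites, and strata cannot be defined until that is settled.
2. In 4.4, have the CRC generate permuted blocks of concealed, varying size within each confirmed centre. Number the boxes by centre, and have the investigator state the centre in the central call before a box is assigned.
3. Include centre as a factor in the primary analysis. Most of the precision gain lies here, and it must accompany stratification because a plain t test would then be conservative (3.8%).

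The cost is one short list per centre in place of one list, and a centre prefix on the labels, fixed before the factory labels the boxes. Incomplete last blocks may move the arms slightly off 40:40, and each centre needs a few spare boxes. If the boxes are already labelled, step 3 alone keeps most of the precision gain but does not prevent a lopsided centre.

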### Blinding and adverse event

4.5

In this trial, the investigators, physicians, nurses, laboratory personnel, statisticians (analyze outcomes), and other participants have no access to the random listing, and will not know the corresponding relations between sequence numbers and different groups until the whole trial is finished (including the statistics). All the researchers will not be in contact with the CRC and the pharmaceutical factory. Additionally, the CRC and pharmaceutical factory will be isolated from all related researchers and participants.

If an adverse event (AE) is reported, researchers should record it immediately and provide a proper emergency treatment, in case of serious adverse event, then report this to the Institutional Review Board within 24 hours. Then, the chief of Longhua Hospital ethic committee, CRC, and the highest investigators will decide to break the blinding or not after a short meeting. If an unblinding decision is made, then the intervention information of this participant, THJG, or THJG placebo will be offered by CRC.

## Outcomes

5

### Primary outcomes

5.1

#### Integral TCM syndrome score (from baseline to week 4)

5.1.1

Integral TCM syndrome score is a widely used system to evaluate the efficacy of Chinese herb treating SCAD patients, which are stagnant Qi and blood type in China.^[11]^ This assessment form is constitutive of 2 parts: symptom part and sign part. In detail, there are total 8 appraisable items, angina, chest distress, palpitation, vexation, insomnia, lassitude, dizziness, and color of lips and snails, respectively. Each item consists of 4 levels and regarding scores. Wholly, the minimum score is 0 and the maximum score is 33. The higher scores of participants mean a severer condition. The scores and details of TCM syndrome are given in Tables 2 and 3.

**Table 2 T2:**
[figure not shown]
Traditional Chinese medicine symptom score.

**Table 3 T3:**
[figure not shown]
Traditional Chinese medicine symptom details.

### Secondary outcomes

5.2

#### Integral TCM syndrome score (from baseline to weeks 2 and 8)

5.2.1

Integral TCM syndrome score from baseline to weeks 2 and 8 will be calculated as one of the secondary outcomes.

#### Inflammation indexes (from baseline to week 4)

5.2.2

We will monitor blood tests to certify if THJG could improve the inflammation condition, including the blood fat, *C*-reactive protein, tumor necrosis factor α, lymphocyte type, complement level, interleukin (IL, including IL-2, IL-6, IL-8, and IL-10), and immune globulin (Ig, including IgA, IgM, and IgG).

#### Seattle Angina Questionnaire (SAQ) (from baseline to weeks 2, 4, and 8)

5.2.3

The SAQ is a disease-specific and functional questionnaire measuring 5 dimensions of health condition with 19 items: exertional capacity, anginal stability, anginal frequency, treatment satisfaction, and disease perception. Each question has 5 choices and regarding 1 to 5 scores (6 for the anginal frequency scale). Groups of studies certify the validity, responsiveness, and reliability of this evaluative instrument. Additionally, it is self-administrated and brief, requiring <5 minutes to complete. The SAQ can offer sensitive and clinically valuable outcome measures in cardiovascular research, widely used in SCAD trials.^[12–14]^

#### Major adverse cardiovascular events (from baseline to weeks 2, 4, and 8)

5.2.4

We will calculate the rate of major adverse cardiovascular events (MACE), which comprised fatal CVDs, nonfatal MI, nonfatal cardiac arrest, nonfatal stroke, and cardiac interventions (percutaneous coronary intervention and coronary artery bypass grafting) from randomization to the end of 8 follow-up completion. This outcome measure is commonly used in clinical trials.^[15–17]^

#### Athens Insomnia scale (from baseline to weeks 2, 4, and 8)

5.2.5

Comprehensive evidence was found that there is a link between insomnia symptoms and CAD.^[18]^ Athens Insomnia scale (AIS) is a frequently used and invaluable global insomnia symptom questionnaire in adolescents, consisting of 8 items: sleep induction, awakenings during the night, early morning awakening, total sleep duration, sleep quality during the night, emotion during the day time, functioning capacity, and sleepiness during the day time. Each item rates 0 to 3 (with 0 regarding to “no problem at all” and 3 “very serious problem”), thus maximum score is 24, which implies the most severe degree of insomnia. The higher score suggests the worse sleep quality.^[19]^

#### 36-Item short form health survey (from baseline to weeks 2, 4, and 8)

5.2.6

The 36-item short form health survey (SF-36) is a generic health status tool for measuring physical status of SCAD patients.^[20,21]^ The SF-36 consists of 36 items with 8 subscales, including physical function, role physical, bodily pain, and global health, vitality, social function, role emotional, and mental health.^[22]^

### Safety assessments

5.3

To assure the safety of participants, the patients’ blood routine, urine routine, feces routine, kidney and liver function, brain natriuretic peptide (BNP), echocardiography, and electrocardiograph will be tested on schedule. Patients will also be asked about several of adverse effects at each visit. When an AE is claimed, researchers will record it and provide an appropriate treatment, then report them to the Institutional Review Board within 24 hours. We also will figure out the real causes of all AEs.

To protect patients’ privacy, all participants will be visited in a closed room. Participants can raise questions and withdraw at any time.

### Participant timeline

5.4

Recruitment will start in October 2019 and end in January 2021. The last visit will be finished before January 31, 2021. The recruitment process is shown in Figure 1, and the schedule is given in Table 4.

**Figure 1 F1:**
[figure not shown]
Project overview. SCAD = stable coronary artery disease, THJG = Taoren Honghua Jian granule.

**Table 4 T4:**
[figure not shown]
Schedule of enrollment and assessments (a separate Word file).

### Data collection and monitoring

5.5

In this 8-weeks’ trial, all participants will be treated with THJG or THJG placebo for 4 weeks and followed-up for another 4 weeks. Five rounds (the baseline, week 2, week 4, and week 8) of disease evaluations and safety evaluations, and 2 rounds (the baseline, and week 4) blood examinations will be recorded in CRFs at each visit point, then entered in Epidata software (Version 3.1) by 2 statisticians independently every month. Difference will be solved by discussion and a 3rd party. All the trained data processors come from the CRC to keep the quality of data collection.

### Quality control

5.6

Longhua Hospital affiliated with Shanghai University of Traditional Chinese Medicine (http://www.longhua.net/ywsy/gzlc/287.jhtml) is responsible for quality controlling and training for all investigators.

At the beginning of this trial, physicians, nurses, and laboratory personnel from 3 research centers will receive systematic training together to completely apprehend the procedure of the whole study. As the trial starts, a trained investigator will be sent to each center every week to check the following:

(1)Number of recruited participants in each center.(2)Included SCAD patients meet the inclusion criteria and do not meet the exclusion criteria.(3)All the participants have signed the informed consent and follow the study process.(4)Clinicians have written the CRFs in time.

### Sample size calculation

5.7

We conducted a pre-experiment of THJG and placebo treating SCAD from June 2018 to December 2018. According to the formula, 

, N1 and N2 are the patient numbers in THJG group and placebo group; *Z*_1–*α*_ = 1.96 when *α* = 0.05; *Z*_1–*β*_ = 1.282 when 1 − *β* = 0.90; *σ* (standard deviation of 2 groups) = 7.7; *k* = 1; *μ*_*r*_–*μ*_*c*_ (the difference of integral TCM syndrome score of THJG and control group) = 4; Δ = 0. Therefore, we plan to recruit 80 participants in total (40 of them in each group) to achieve a 90% power and a 2-sided 5% significance level in detecting the therapeutic differences between 2 groups.

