### Statistical analysis

5.8

A trained statistician from CRC will complete all the statistical analysis, by Statistical Packages of Social Sciences software (version 24.0). Intention-to-treat approach for effectiveness and safety analysis will be used. As dealing the missing values, last-observation-carried-forward method will be applied. The mean ± standard deviation will be chosen for the description of continuous variables and the percentage is chosen to describe the variable values. Continuous variables, which are kept in the normal distribution, will be analyzed by Student *t* test; or else, nonparametric tests will be adopted. All statistical tests are 2-sided and *P* < 0.05 means statistically significant.

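### The stated inputs require 78 patients per group, not 40; at 40 per group the power for a 4-point difference is about 63%, not 90%

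*Protocol article*

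**What the plan says.** The calculation is in section 5.7 (Sample size calculation) of the protocol article. The formula itself is not legible in the text available, but every input is given:

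- significance level: "1.96 when *α* = 0.05", described as "a 2-sided 5% significance level in detecting the therapeutic differences between 2 groups"
- power: "1.282 when 1 − *β* = 0.90"
- standard deviation: "standard deviation of 2 groups) = 7.7"
- target difference: "the difference of integral TCM syndrome score of THJG and control group) = 4"
- allocation ratio k = 1 and margin Δ = 0

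The conclusion drawn is: "Therefore, we plan to recruit 80 participants in total (40 of them in each group) to achieve a 90% power".

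The analysis that this sample size must support is in section 5.8 (Statistical analysis): "Continuous variables, which are kept in the normal distribution, will be analyzed by Student *t* test". All tests are two-sided, and no baseline adjustment is mentioned. The primary outcome (section 5.1.1) is the integral TCM syndrome score from baseline to week 4.

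**The concern.** A difference of 4 with a standard deviation of 7.7 is a standardised effect of 4 / 7.7 = 0.519. Forty per group is visibly too few to detect an effect of that size with 90% power in a two-sided 5% test. The planned total is about half of what the inputs imply.

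What is at stake is how the result can be read. A trial with 90% power for its target difference misses a true effect of that size one time in ten; a trial with 63% power misses it more than one time in three. The Discussion (section 6) expects the trial to settle whether the product works. A reader who trusts the published 90% could take a non-significant result as good evidence against a 4-point benefit, which the design could not support. Ethics committees and readers are also given an operating characteristic that the trial does not have.

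**Working it through.** **Inputs (all from section 5.7):** Z for two-sided α = 0.05 is 1.96; Z for 90% power is 1.282; σ = 7.7; difference = 4; k = 1; Δ = 0; planned n = 40 per group. Test: unadjusted two-sample t test (section 5.8).

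**1. Required sample size.** For two independent means,

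n per group = (1 + 1/k) × [σ × (Z₁ + Z₂) / (difference − Δ)]²

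- Z₁ + Z₂ = 1.96 + 1.282 = 3.242
- 7.7 × 3.242 / 4 = 6.241, and 6.241² = 38.95
- (1 + 1/1) × 38.95 = 77.9, rounded up to **78 per group, 156 in total**

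The exact t-test calculation gives 79 per group (158 in total); 78 per group falls just short, at 89.7%.

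**2. Can the stated 40 per group be reproduced?** Changing one or both of the usual settings does not do it:

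| Setting | n per group |
|---|---|
| Two-sided 5%, 90% power (as stated) | 78 |
| One-sided 5%, 90% power | 64 |
| Two-sided 5%, 80% power | 59 |
| One-sided 5%, 80% power | 46 |
| As stated, without the factor (1 + 1/k) = 2 | 38.9, so 39 |

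Of these, only the last line comes close to 40. Taking the per-group 78 as the trial total leads to the same place: 78 / 2 = 39 per group. Either slip, rounded up, would give 40 and 80. This explanation is an inference, because the formula is not visible.

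**3. Power at 40 per group.**

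- Standard error of the difference: 7.7 × √(2/40) = 1.722
- Difference over standard error: 4 / 1.722 = 2.323
- Normal approximation: Φ(2.323 − 1.96) = Φ(0.363) = **64.2%**
- Two-sample t test (noncentral t, 78 degrees of freedom): **63.1%**, so a type II error of about 37%

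**4. What 40 per group can detect (t test, σ = 7.7).**

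- 90% power: 5.65 points (normal approximation 3.242 × 1.722 = 5.58)
- 80% power: 4.88 points
- Standard deviation at which 40 per group would give 90% power for 4 points: 5.45
- Expected half-width of the 95% confidence interval: 1.991 × 1.722 = 3.4 points

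**The case against.** **The formula cannot be seen.** This is a gap in the text extraction and no fault of the protocol. It limits what can be said about the cause of the error, but not the mismatch: the inputs, the two-group design and the conclusion are all stated.

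**The meaning of 7.7 is not stated.** This is the strongest objection. Section 5.7 does not say whether 7.7 describes scores at one time point or changes from baseline. If it describes single-time scores and change is analysed, the standard deviation of change is 7.7 × √(2(1 − r)), where r is the correlation between baseline and week 4. The protocol does not give r, so these values are assumptions: for 40 per group, r = 0.5 leaves power at 63%, r = 0.7 gives 84%, and r = 0.75 gives 90%. With baseline adjustment, r = 0.7 would give 89%. So 63% is conditional on 7.7 being the standard deviation of the analysed variable. That does not rescue the claim as written. Section 5.7 makes no such argument and puts 7.7 directly against the 4-point difference, and section 5.8 names an unadjusted test. If 7.7 is already the standard deviation of change, the gain in analysing change has been used.

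**Details may sit in a full protocol or analysis plan.** That would answer an omission. Here a stated figure contradicts its own stated inputs, and no further document can make 40 follow from them. For the same reason nothing is made here of a dropout allowance: an article may leave it out, and the shortfall exists with complete data.

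**A null result may not be misread.** True: the protocol does not say how it would interpret one. The risk lies in the published 90%, which invites the misreading.

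**Conclusion.** The concern holds. With the inputs of section 5.7, 90% power at two-sided 5% requires 78 per group (79 by the exact t test), about twice the planned 40. The planned trial has about 63% power for the 4-point target by the t test (64% by the normal approximation). It reaches 90% only for a difference of about 5.65 points.

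The required number is arithmetic on stated figures. The 63% rests on two further conditions: that 7.7 is the standard deviation of the variable analysed, and that the test is the unadjusted t test of section 5.8. The proposed cause, a lost factor of 2 or a per-group number read as a total, is likely but unproven, and the conclusion does not depend on it. This must be corrected, because the stated power for the primary outcome is wrong.

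**What to change.** Keep N = 80 and replace the concluding sentence of section 5.7 with text such as:

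> With 40 patients per group, a standard deviation of 7.7 and a two-sided 5% t test, the trial has about 63% power to detect a 4-point difference; 90% power applies to a difference of about 5.7 points. A non-significant result will be reported through its 95% confidence interval and treated as inconclusive, not as evidence of no effect.

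Delete the 90% claim for 4 points, and state whether 7.7 is the standard deviation of the week-4 score or of the change from baseline.

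The cost is one paragraph and a less favourable stated power. It needs no extra patients and changes nothing clinical.

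This corrects the claim but not the power. If the sponsor wants 90% power for 4 points, the consistent alternatives are to enlarge the trial to 156 to 158 patients, which was still open when the article described recruitment as yet to start, or to prespecify a baseline-adjusted analysis with a documented correlation. On the second route, 40 per group would need a correlation of about 0.71, from √(1 − (5.45 / 7.7)²), with 7.7 as the standard deviation of the unadjusted score.
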